## Abstract

**Background:**

Colorectal cancer is the second most common cancer and cancer-killer in Hong Kong with an alarming increasing incidence in recent years. The latest World Cancer Research Fund report concluded that foods low in fibre, and high in red and processed meat cause colorectal cancer whereas physical activity protects against colon cancer. Yet, the influence of these lifestyle factors on cancer outcome is largely unknown even though cancer survivors are eager for lifestyle modifications. Observational studies suggested that low intake of a Western-pattern diet and high physical activity level reduced colorectal cancer mortality. The Theory of Planned Behaviour and the Health Action Process Approach have guided the design of intervention models targeting a wide range of health-related behaviours.

**Methods/design:**

We aim to demonstrate the feasibility of two behavioural interventions intended to improve colorectal cancer outcome and which are designed to increase physical activity level and reduce consumption of a Western-pattern diet. This three year study will be a multicentre, randomised controlled trial in a 2x2 factorial design comparing the “Moving Bright, Eating Smart” (physical activity and diet) programme against usual care. Subjects will be recruited over a 12-month period, undertake intervention for 12 months and followed up for a further 12 months. Baseline, interim and three post-intervention assessments will be conducted.

Two hundred and twenty-two colorectal cancer patients who completed curative treatment without evidence of recurrence will be recruited into the study. Primary outcome measure will be whether physical activity and dietary targets are met at the end of the 12-month intervention. Secondary outcome measures include the magnitude and mechanism of behavioural change, the degree and determinants of compliance, and the additional health benefits and side effects of the intervention.

**Discussion:**

The results of this study will establish the feasibility of targeting the two behaviours (diet and physical activity) and demonstrate the magnitude of behaviour change. The information will facilitate the design of a further larger phase III randomised controlled trial with colorectal cancer outcome as the study endpoint to determine whether this intervention model would reduce colorectal cancer recurrence and mortality.

**Trial registration:**

ClinicalTrials.gov No: NCT01708824

## Background

### Colorectal cancer, treatment outcome and lifestyle factors

According to the Hong Kong Cancer Registry [1], colorectal cancer (CRC) was the second most common cancer and the second highest cancer-killer in Hong Kong with 4,370 new cases and 1,864 deaths in 2010, respectively. Moreover, the crude incidence rate of CRC increased from 48.2 per 100,000 in 2000 to 62.2 per 100,000 in 2010 [1]. CRC may soon become the most common cancer in Hong Kong. This alarming trend is mirrored in many Asian countries [2].

The latest report of the World Cancer Research Fund (WCRF) [3] summarises convincing evidence from published observational studies that physical activity (PA) protects against colon cancer (CC) while foods low in dietary fibre, high in red and processed meat, high levels of alcohol drinking in men, body fatness, abdominal fatness and factors leading to greater adult attained height cause CRC. However, the influence of these lifestyle factors on the outcome of patients with established CRC is largely unknown.

With advances in treatment, CRC survivors are now living longer. Many of them are highly motivated to seek information about lifestyle modifications that improve quality of life and increase their chance of prolonged life and recovery from cancer. Although evidence on certain aspects of PA or diet specifically affecting health outcomes in cancer survivors is emerging, it is not yet sufficiently established to allow firm recommendations to be made [4].

The observational Nurses’ Health Study showed that recreational PA reduced cancer-specific and overall mortality for stage I to III female CRC patients [5], while in another observational study [6], maintaining weekly PA levels over 18 metabolic-equivalent-hours (MET-hours) reduced recurrence and mortality in stage III CC after adjuvant chemotherapy.

A recent observational study compared cancer outcome of stage III CC in two dietary groups [7]. Compared with patients with the lowest mean intake of a Western-pattern diet (i.e., 2.3 servings of red meat weekly, 1.8 servings of processed meat weekly, 2.0 servings of refined grains daily, and less than 1 serving of sugary desserts daily), those with the highest mean intake (i.e., 6 servings of red meat weekly, 5.6 servings of processed meat weekly, 5.8 servings of refined grains daily, and 2.5 servings of sugary desserts daily) had an adjusted hazard ratio for death of 3.25 (95% confidence interval 2.04-5.19). No association was found of a prudent dietary pattern (i.e., high intakes of fruit, vegetable, poultry and fish) with CC mortality and recurrence. Moreover, the two patterns were not inter-correlated (Spearman correlation 0.02).

Our literature review identified a small number of published randomised controlled trials (RCT) or feasibility studies [8-12] on lifestyle intervention of CRC survivors. No CRC intervention has been conducted in an Asian population. Furthermore, to date, there are no published data regarding the effect of PA and/or dietary interventions on CRC outcomes.

### Theories on health behaviour

The Theory of Planned Behaviour (TPB) [13] is one of the most widely tested theories explaining and predicting intentions to perform a wide range of health-related behaviours [14-18]. The TPB has been the framework for the design of intervention models targeted at health behaviour change [19,20] and posits that an individual’s behaviour is predicted by his/her intention to perform the behaviour. This behavioural intention is, in turn, determined by attitudes towards the behaviour, subjective norms, and perceived behavioural control, with each of these being the result of beliefs. The likelihood that an individual’s intention to adopt a health behaviour will therefore be increased if he holds a more favourable attitude towards the behaviour (behavioural beliefs), believes that significant others want him to adopt the behaviour (normative beliefs), and perceives that the behaviour is under his control (control beliefs). The three sets of belief constructs can thus be targeted by interventions for health behaviour change. Useful as the TPB is, it is important to note that intentions to behave do not necessarily lead to actual performance of behaviours. The discrepancy between intended and actual behaviours is termed the intention-behaviour gap [21].

The Health Action Process Approach (HAPA) [22] integrates social-cognitive theory [23], the theory of reasoned action [24] and the volition theories [25,26]. HAPA is particularly useful in guiding the development and design of intervention aimed to enhance health self-regulation [27] that involves motivation, volitional, and actional processes of abandoning health-compromising behaviours and adopting and maintaining health-enhancing behaviours [28]. The model addresses the intention-behaviour gap and defines ways to identify and modify the factors linking intentions with actual behaviour (mediators). The model categorizes health behavioural changes into two stages (processes): the pre-intentional motivation process and the post-intentional volition process, with the first process leading to behavioural intention and the second to actual health behaviours [27]. After a person has an intention to act, he/she needs detailed instructions on how to perform the desired action and the perceived self-efficacy to initiate and to maintain the action. All these require self-regulatory skills and strategies such as action planning [22]. Interventions for changing health behaviours can target attitudes, perceived barriers, personal vulnerability and perceived self-efficacy, however, only stage-matched conditions can bring about benefits on the participants. For example, only intenders and actors will benefit from self-regulatory efforts.

### Study objectives

Based on the TPB and HAPA, this study aims to evaluate the acceptability and feasibility of two behavioural interventions on CRC survivors intended to improve cancer outcome and are designed to increase PA levels and reduce consumption of a Western-pattern diet (i.e., high intake of red and processed meat, dietary fat, refined grains and sugary desserts) [7,29].

## Methods/design

Ethical approval for the study has been received from the Institutional Review Board of the Hong Kong West Cluster, the Hospital Authority in Hong Kong (see later). All participants will receive a written participant information sheet explaining the trial and all will be asked to give written consent prior to participation.

### Study/trial design

This will be a three-year multicentre, randomised controlled trial (RCT) following a 2x2 factorial design comparing PA and dietary interventions with usual care in CRC patients.

A 2x2 factorial design is chosen because it has the advantage of testing both interventions with a smaller sampler size when compared with the alternative of a three parallel group design.

### Treatment period and follow up

Dietary and PA interventions will be delivered over a 12 month period and participants will be followed up for a further 12 months.

Baseline assessment will be conducted at the University of Hong Kong. All baseline measures will be made prior to group allocation. An interim outcome assessment will be performed six months after randomization. Outcome/follow-up assessments will be made at 12, 18 and 24 months after randomization. Staff responsible for outcome assessment will not deliver the intervention. All outcome assessments will be subject to a strict protocol with researchers blinded to group allocation.

All participants (including the usual care group) will be given written, publicly-available general advice that encourages healthy lifestyles.

Participants in the PA intervention group will have one face-to-face intervention contact at the beginning followed by fortnightly telephone contacts for 12 months. They will also receive 12 stage-based information pamphlets and four newsletters by mail and will attend four group meetings during the 12-month intervention period.

Participants in the dietary intervention group will have two face-to-face intervention contacts during the first four months and fortnightly telephone contacts throughout the 12 months. They will also receive 12 stage-based information pamphlets and four newsletters by mail and will attend four group meetings during the 12-month intervention period.

The interventions will be delivered by trained research staff and the research team members.

### Primary outcome

To evaluate the acceptability and feasibility of two behaviour interventions for CRC survivors intended to improve cancer outcome. These interventions are designed to:

1. Increase PA levels to improve general health and cancer outcome;

2. Decrease consumption of a Western-pattern diet.

The PA target for improving general health is 30 minutes of moderate-to-vigorous intensity PA (MVPA) five days a week (equivalent to 10 MET-hours per week). The PA target for improving cancer outcome is 60 minutes of MVPA five days a week (equivalent to 18–20 MET-hours per week).

The dietary targets are to limit weekly red or processed meat intake to <5 servings and to limit daily refined grain intake to two servings.

The primary outcome measure will be whether the PA or dietary targets are met at the end of the 12-month intervention.

### Secondary outcomes

To assess the magnitude of PA and dietary change and estimate the association of such changes with changes in the underlying theoretical constructs (mechanisms of behavioural change).

We will determine:

1. The degree and determinants of compliance to the intervention.

2. The additional health benefits (including body composition, physical fitness, quality of life and mood), and any side effects (including nutritional deficiency and PA-associated injury) of the intervention.

### Measures/assessment instrument

Measures of all outcome points will be completed face-to-face. Details of the outcomes to be collected at different time points and the instruments used are shown in Table 1.

**Table 1 T1:** Outcome measures

	**Measures**	**When**
**Primary outcome**		
PA target – general health	Accelerometer	0 M, 6 M, 12 M, 18 M, 24 M
PA target – cancer outcome	Accelerometer	0 M, 6 M, 12 M, 18 M, 24 M
Dietary target – red/processed meat	FFQ [30]	0 M, 6 M, 12 M, 18 M, 24 M
Dietary target – refined grain	FFQ [30]	0 M, 6 M, 12 M, 18 M, 24 M
**Secondary outcome**		
Magnitude of PA change	Accelerometer	0 M, 6 M, 12 M, 18 M, 24 M
	GPAQ [31]	
Magnitude of dietary change	FFQ [30]	0 M, 6 M, 12 M, 18 M, 24 M
Compliance	Intervention record; pedometer, food diary	6 M, 12 M
Measurement of theoretical constructs	Questionnaire	0 M, 6 M, 12 M, 18 M, 24 M
Facilitators and barriers of intervention	Questionnaire	6 M, 12 M
	Focus-group discussion	Towards end of intervention (last group meeting)
BMI, WHR	Calibrated scales, stadiometer; tape measure	0 M, 6 M, 12 M, 18 M, 24 M
Body and visceral fat	Bioelectrical impedance	0 M, 12 M, 24 M
Physical fitness	Six-minute ergometry	0 M, 12 M, 24 M
Quality of life	SF12 [32,33], FACT [34]	0 M, 6 M, 12 M, 18 M, 24 M
Mood	HADS [35,36], PSS [37]	0 M, 6 M, 12 M, 18 M, 24 M
Dietary deficiency – caloric and protein intake	FFQ [30]	0 M, 6 M, 12 M, 18 M, 24 M
Dietary associated anaemia	CBC by blood test	0 M, 6 M, 12 M, 18 M, 24 M
PA- associated injury	Direct questioning during phone call	Fortnightly during intervention, 6 M, 12 M

Abbreviations: M-months post-randomization, PA-physical activity, BMI-body mass index, WHR-waist-hip ratio, FFQ-food frequency questionnaire, GPAQ-global physical activity questionnaire, SF12-Short Form 12 item, FACT-Functional Assessment of Cancer Therapy, HADS-Hospital Anxiety and Depression Scale, PSS-Perceived Stress Scale, CBC-complete blood count.

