### The usual care (control) group

Similar to those in the intervention groups, the usual care participants will be mailed, at regular intervals, five pamphlets containing general advice encouraging a healthy lifestyle, including eating a wide variety of food, eating more fruit and vegetable, increasing physical activity level, maintaining a normal body weight, quitting smoking and avoiding alcohol abuse. The above mentioned information is widely available in the public domains (websites of the World Health Organization and the Department of Health in Hong Kong).

Maintaining contact with these participants from the baseline assessment to the various outcome assessments is done to minimize loss to follow-up. Furthermore, this practice would ensure that all participants receive some lifestyle advice that at the moment is given on an ad hoc basis. We anticipate that the effect of these pamphlets alone would be small.

Figure 1 illustrates the participant pathway throughout the trial.

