### Serious adverse events and adverse events

No serious adverse events (SAE) are anticipated. However, if any SAE occurs, this will be reported to the Institutional Review Boards and will also be drawn to the immediate attention of the clinical collaborators of the participating departments.

Participants receiving the dietary intervention will be monitored to prevent specific nutrient deficiency including inadequate caloric and protein intakes and iron-deficiency anaemia due to inadequate red meat intake. Participants receiving the PA intervention will be monitored for PA-associated injury.

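### PA-associated injury is a secondary outcome, but its collection depends on the arm, so any between-arm injury comparison would tend to overstate injury with the PA intervention

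*Protocol article*

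**What the plan says.** All references are to the protocol article.

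- **Status.** Secondary outcomes includes "any side effects (including nutritional deficiency and PA-associated injury) of the intervention", and Table 1 places injury in its secondary-outcome block.
- **Instrument and schedule.** Table 1 gives "Direct questioning during phone call" and "Fortnightly during intervention, 6 M, 12 M".
- **Contacts by arm.** Under Treatment period and follow up, the PA group has "one face-to-face intervention contact at the beginning followed by fortnightly telephone contacts for 12 months" and the dietary group has "two face-to-face intervention contacts during the first four months and fortnightly telephone contacts throughout the 12 months". For the control group, "the usual care participants will be mailed, at regular intervals, five pamphlets containing general advice encouraging a healthy lifestyle"; no telephone calls are described.
- **Who is monitored.** Serious adverse events and adverse events states: "Participants receiving the PA intervention will be monitored for PA-associated injury". It says nothing about injury in the other arms.
- **Mode and blinding.** Measures/assessment instrument says "Measures of all outcome points will be completed face-to-face". Treatment period and follow up says that outcome assessors are blinded and do not deliver the intervention.
- **Analysis.** Main analysis assigns secondary outcomes to mixed-effects models and makes no exception for injury.

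**The concern.** How often a participant is asked about injury, and by whom, depends on the randomised arm. The fortnightly calls are listed as components of the PA and dietary interventions, so the person asking is delivering the intervention and knows the allocation. The other side-effect rows in Table 1 (caloric and protein intake, blood count) have fixed visits from 0 to 24 months. Injury is the only one tied to intervention contact.

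More frequent asking finds more minor injuries. If the reports from all sources were compared between arms, PA would appear to cause some injuries that were simply better recorded. The trial is meant to inform a phase 3 design, so a distorted injury contrast could be carried forward. Later analysis cannot recover injuries that usual-care participants were never asked about.

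**Working it through.** The document gives no figure for injury, so there is no stated result to reproduce. The check counts enquiries and then shows how large a spurious contrast could be under stated assumptions.

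**Step 1: enquiries in 12 months.**
- PA arms: 52 weeks / 2 = 26 calls, plus 6 and 12 months.
- Usual care: at most 2 (6 and 12 months). If the telephone instrument and the PA-only monitoring sentence are both taken literally, 0.
- Diet-only arm: also 26 calls, but the article does not say whether they ask about injury.

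**Step 2: spurious risk ratio.** Assumptions, none from the document: equal true 12-month injury risk r in all four cells; calls capture every injury; a fraction s is recalled where only the six-monthly visits ask.

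- PA-only against usual care: r / (r × s) = 1/s.
- PA margin (both PA cells against both non-PA cells), diet calls ask: r / [r(1 + s)/2] = 2/(1 + s).
- PA margin, diet calls do not ask: r / (r × s) = 1/s.

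| s | PA-only vs usual care | PA margin, diet calls ask | PA margin, diet calls do not ask |
|---|---|---|---|
| 0.9 | 1.11 | 1.05 | 1.11 |
| 0.7 | 1.43 | 1.18 | 1.43 |
| 0.5 | 2.00 | 1.33 | 2.00 |
| 0.3 | 3.33 | 1.54 | 3.33 |

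The true ratio is 1.0 throughout. If usual care is not asked at all, there are no control data and no ratio can be formed.

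**Step 3: what a test would do.** The Sample size section gives 50 per cell, so 100 against 100 at the PA margin. Take r = 10% and s = 0.5, again as assumptions.
- Diet calls do not ask: observed risks are 10% and 10% × 0.5 = 5%. A nominal 5% test would be significant about 27% of the time with no true difference.
- Diet calls ask: observed risks are 10% and 10% × (1 + 0.5)/2 = 7.5%, significant about 9% of the time.

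**Step 4: the mode of collection.** The fortnightly calls are not outcome points, so they do not conflict with the face-to-face statement. The 6- and 12-month entries in the same row are outcome points. There the listed instrument is a telephone call while the general rule is face-to-face, so those entries need reconciling.

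**The case against.** The strongest reply is that no between-arm injury comparison is stated. The adverse-event section reads as safety monitoring within the PA arms. The secondary-outcome block of Table 1 also holds rows that make sense mainly in intervention arms, such as compliance and the focus groups, and the mixed-effects sentence is one generic line. The schedule already lists 6 and 12 months, when all participants are seen by blinded assessors.

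Much of this stands, and it rules out three stronger readings that a reader might infer:

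- *That a biased comparison is planned.* It is implied by secondary-outcome status and the general analysis sentence, but not spelled out. That usual care receives no calls is likewise inferred from the contact descriptions, not stated as an exclusion.
- *That the safety findings would be uninterpretable.* The injury rate within closely monitored PA arms is interpretable and relevant to feasibility, and the bias would tend to overstate harm rather than hide it.
- *That telephone collection flatly contradicts the face-to-face rule.* It does so only for the 6- and 12-month entries.

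The reply does not remove the point. Injury is labelled a secondary outcome, nothing limits a comparison to 6 and 12 months, and the only instrument listed for those visits is a telephone call. An unseen analysis plan could restrict the analysis, but it could not supply answers to a question that was not asked.

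**Conclusion.** The point holds in a limited form. As Table 1 is written, injury ascertainment depends on the arm, and any between-arm comparison using all the reports would tend to overstate injury with PA, or would have no control data. The direction rests on one assumption: that recall over six months is less complete than recall over two weeks. The size cannot be known from the document. The range of 1.11 to 3.33 is for PA-only against usual care and depends on the assumed recall and on full capture by the calls. At the PA margin the range is 1.05 to 1.54 if diet-arm calls also ask, and the same 1.11 to 3.33 if they do not. This is worth correcting because it is cheap. It does not touch the primary outcome or the sample size.

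**What to change.** Split the injury row of Table 1 in two.

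1. **Comparative outcome:** the same injury question, asked face-to-face by the blinded assessor at the existing 6- and 12-month visits in all four arms. Only these answers enter any between-arm comparison.
2. **Safety monitoring:** injury reports from the fortnightly calls, described within the intervention arms only. State whether the diet-arm calls ask about injury.

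Then reconcile Table 1 with Treatment period and follow up, Measures/assessment instrument, and Serious adverse events and adverse events, so that they agree on who is asked, how and by whom. If no between-arm comparison is intended, label the row as monitoring within the PA arms.

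The cost is at most one question at visits already scheduled, plus a table edit; no sample size changes. With equal recall and equal true risk, the expected ratio returns to 1.0. Two limits remain: minor injuries between visits will be under-recalled, and participants prompted every fortnight may still recall somewhat more at 6 and 12 months. The bias is reduced, not fully removed.

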### Centre and participant selection

Participants will be recruited from the surgical and clinical oncology departments of four public hospitals (Queen Mary Hospital, Pamela Youde Nethersole Eastern Hospital, Princess Margaret Hospital and Yan Chai Hospital) in three regions of Hong Kong. The intervention will be delivered in the three regional centres (Queen Mary Hospital on Island West, Pamela Youde Nethersole Eastern Hospital on Island East and Princess Margaret Hospital at Kowloon West). The clinical collaborators of each site have established that the colorectal and oncology teams are willing to participate in this trial.

